## Abstract

**Background:**

Non-typhoidal Salmonella (NTS) are a major cause of bloodstream infections amongst children in sub-Saharan Africa. A clear understanding of the seroepidemiology and correlates of protection for invasive NTS (iNTS) in relation to key risk factors (malaria, anaemia, malnutrition) in children in Africa is needed to inform strategies for disease control including vaccine implementation.

**Methodology:**

The SAiNTS study is a prospective community cohort study with paired serology samples from 2500 Malawian children 0–5 years at baseline and three months to measure age-stratified acquisition of lipopolysaccharide (LPS) O-antigen antibody (IgG) and serum bactericidal activity to the main serovars causing iNTS (
*Salmonella* Typhimurium and
*S*. Enteritidis). Children are selected from mapped and censused randomly selected households in Chikwawa, Malawi; an area with substantial malaria burden. The sampling framework is set within a malaria vaccination (RTS,S/ AS01) phase 4 cluster randomized trial, known as the Epidemiology Study of Malaria Transmission Intensity (EPI-MAL), allowing exploration of the impact of malaria vaccination on acquisition of immunity to NTS. Risk factor data for invasive disease will be collected using rapid diagnostic tests for malaria and anaemia, anthropometry for malnutrition, and a validated questionnaire for indicators of socioeconomic status, water and sanitation. All data will be recorded through electronic case report forms using the REDCap and the Open Data Kit (ODK) platforms. Stool sample analysis includes NTS culture and pan-Salmonella polymerase chain reaction to assess enteric exposure and biomarkers of environmental enteric dysfunction. Cases with iNTS disease will be followed up for comparison with community controls.

**Conclusions:**

The final cohort of 2500 children will allow investigation into the impact of risk factors for iNTS on the acquisition of immunity in children 0–5 years in an endemic setting, including comparisons to partner seroepidemiology studies in three other sub-Saharan African sites (1000 children per site). The data generated will be key to informing iNTS disease control measures including targeted risk factor interventions and vaccine implementation through investigation of correlates of protection and identifying windows of immune susceptibility in at-risk populations.

## Introduction

Invasive Salmonella infection (both typhoidal and non-typhoidal serovars) are a major cause of mortality and morbidity worldwide
^
1
^. Non-typhoidal strains of Salmonella (NTS) are an important cause of enterocolitis, with an estimated disease burden of 95 million cases in 2017, but with a low case-fatality rate (CFR). However, non-typhoidal salmonella infections can be invasive, causing bacteraemia, meningitis and other focal infections. Cases, predominantly in children under five years of age, present with non-specific febrile illness and have a high CFR
^
2
^. Invasive NTS (iNTS) disease is also associated with poor nutritional status, younger age, immune-suppression and severe malarial anaemia
^
1
^. Invasive NTS is most commonly seen in Sub-Saharan Africa (SSA), where certain serovars are endemic within populations.

Progress in controlling iNTS infections are hampered by non-specific clinical presentation, lack of accurate diagnostics, and incomplete knowledge of transmission pathways within the community and correlates of protection.

### Vaccine development

There is no currently licensed vaccine available against iNTS disease. Three iNTS vaccines are now in clinical stages of development. One is a trivalent lipopolysaccharide-flagellin conjugate, targeting typhoid and the two commonest iNTS serovars in Africa
^
3
^. A second is another trivalent conjugate vaccine developed by the International Vaccine Institute (IVI) and supported by Wellcome Innovations
^
4
^. The third is a novel parenteral bivalent iNTS vaccine based on Generalized Modules for Membrane Antigen (GMMA), also targeting serovars Typhimurium and Enteritidis
^
5
^.

**
*The VacciNTS consortium – accelerating a novel iNTS vaccine*
**

GMMA has a unique and robust technical production platform offering high yields at a low cost as compared to other iNTS vaccines. The VacciNTS consortium has recently been funded by a European Union H2020 grant and aims to accelerate WHO prequalification and licensure of this vaccine and vaccine deployment in SSA where the burden of iNTS disease is greatest (
Figure 1). The highly cost-effective GMMA-technology is based on outer membrane blebs released by genetically modified bacteria. Supporting activities include cross-sectional sero-epidemiological studies in potential future phase 2 and 3 clinical trial sites in Malawi, Ghana, Burkina Faso and Kenya (WP7); assessment of the global burden of disease using different risk-based modelling methodologies, and stakeholder engagement and advocacy activities (WP8); and assessments of the cost of iNTS illness and cost-effectiveness of iNTS vaccine introduction (WP9). GSK Vaccines Institute for Global Health (GVGH) are providing the laboratory training and support for the sero-epidemiology studies.

**Figure 1. f1:**
[figure not shown]
Overall Vacc-iNTS strategy.

**
*VacciNTS study sites*
**

Malawi; The rural district of Chikwawa, Southern Malawi, has high seasonal rainfall, humidity, and temperature, and low altitude. Most of the population rely on subsistence farming and over half of households have food insecurity. It is the site of the Epidemiology Study of Malaria Transmission Intensity (EPI-MAL) RTS,S/AS01 malaria vaccine cluster randomised trial, and FIEBRE fever surveillance study.

Burkina Faso; Two sites: 1. Polesgo and 2. Nioko II informal settlements in the Nongr-Massom health district, which are both part of the Ougadougou Health and Demographic Surveillance System (HDSS), and passive fever surveillance for Salmonella since 2011.

Kenya; Three sites: 1. Mukuru Slums (informal settlements), 20km East of Nairobi, 2. Lwak mission hospital (rural, agricultural population), Kisumu County, Western Kenya, 3. Kilifi County Hospital (KCH) rural population part of Kilifi HDSS.

Ghana; Two sites: 1. Agogo Presbyterian Hospital (APH), Asante Akim North Municipal district largest referral hospital in the district serving semi-urban and rural populations. 2. Komfo Anokye Teaching Hospital (KATH) and the Maternal and Child Hospital (MCHH) Kumasi (second largest city in Ghana), Ashanti region. KATH serves as a referral hospital for the northern part of Ghana.

A separate core-protocol
^
6
^ (Extended data) has been written for all sites. This article will focus on the Malawi site protocol due to more complex study design.

**
*Immune correlates of protection on the pathway to vaccine licensure*
**

The gold standard for vaccine licensure and policy decisions are double-blind placebo-controlled randomized trials to determine vaccine efficacy with clinical endpoints. However, this can be prohibitively expensive and a major logistic undertaking requiring very large sample sizes if the clinical endpoint is uncommon and expensive to diagnose, as is the case for iNTS. Immune correlates of protection (CoP) can accelerate the development of vaccines, providing non-clinical pivotal end points in vaccine studies
^
7,
8
^. CoP can be defined as immune markers shown to correlate statistically with a reduced risk of disease
^
9
^.

Estimating an easily measured, robust antibody CoP would be a key step in accelerating any iNTS vaccine towards licensure and deployment.

### Immunological basis for disease

**
*Immunological susceptibility and risk-factors for iNTS disease*
**

iNTS disease has a bimodal age distribution in SSA, being commonest in adults with HIV, and in young children
^
10
^, among whom the median age of invasive disease is 13 months (
Figure 2A and 2B)
^
11
^. iNTS disease is linked to several underlying susceptibilities among children, particularly recent malaria, severe malarial anaemia and malnutrition
^
12
^. Children between the ages of six months to two years are particularly at risk, suggesting protection before six months by breastfeeding and transferred maternal antibody
^
13,
14
^.

**Figure 2. f2:**
[figure not shown]
**A**: Age distribution of iNTS cases (0–60 months).
**B**: Age distribution of anti S. Typhimurium LPS antibodies
^
11
^.

**
*The acquisition of natural immunity to iNTS*
**

**Enteric exposure to iNTS**

Systemic natural protective immunity to iNTS, which is largely acquired between six months - three years in Malawi, develops following exposure of the gastrointestinal (GI) tract to Salmonella. A longitudinal study of a cohort of 50 healthy Malawian children, who were sampled monthly, showed that between the ages of six-18 months more than 50% had at least one episode when a non-typhoidal strain of Salmonella was detected in their stool. Most of these episodes were not associated with current or recent diarrhoea. In any month, there was an 8–9% chance of stool positivity for Salmonella. Quantitative PCR using a pan-Salmonella marker (TTR, tetrathionate reductase gene) was more sensitive than culture for detection
^
15
^. Among samples that were culture-positive, 48% of isolates comprised ST313
*S. *Typhimurium, with the remainder being a wide range of non-typhoidal serovars that are not seen from blood cultures in Malawi. We have termed these enteric infection/exposure events “eNTS” events (unpublished work [name] PhD Thesis:
https://livrepository.liverpool.ac.uk/2010084).

**The acquisition of natural systemic immunity**

We have described the age-stratified sequential acquisition of CD4 cellular immunity, followed by functional antibody-mediated immunity and serum bactericidal activity (SBA) against iNTS among children in Malawi
^
11
^. This demonstrated the nadir of functional humoral immunity, which occurs after the waning of maternal antibody, but before the sequential acquisition of first cellular immunity, then anti-LPS IgG antibody and associated functional SBA. This nadir coincides with the peak incidence of iNTS disease among children at nine-13 months, further demonstrating how a serological protective threshold of humoral protection develops following eNTS exposure over time.

Robust defence against iNTS requires both cellular and humoral immunity, and we have previously demonstrated both cellular and humoral defects that cause susceptibility to iNTS disease. Humoral and cellular defences have both been shown to be impaired in current and recent uncomplicated malaria
^
16
^. Bound, complement-opsonised antibody is required both for SBA, and for uptake of bacteria by phagocytes prior to killing by respiratory burst.

There are critical current knowledge gaps in our understanding of the relationship of enteric Salmonella exposure and the development of protective immunity amongst those in the highest risk age bands; of what are the correlates of protection for iNTS disease; and of how the effect of known susceptibility risk factors in different populations affect these relationships.

Several mechanisms of humoral and cellular immunity are required for protection against iNTS disease, and different risk factors act on different elements of the immune response. This means that some of the resultant background immunological susceptibilities might be fully vaccine-responsive (e.g. a lack of sufficient protective antibody), while others might not be fully ameliorated by vaccine-induced immunity (e.g. periods of complement deficiency, or failure of respiratory burst due to haemosiderin damage to phagocytes). This means that the potential impact of vaccine deployment to prevent iNTS disease might be different in different epidemiological settings.

Understanding these influences will ultimately allow us to understand the effects of specific known risk factors, and to describe antibody correlates of protection. This will allow us to accelerate vaccine licensure and deployment, and to model predicted vaccine impact among different susceptible populations in SSA.

### Model of exposure and immunity

We therefore present a theoretical framework (
Figure 3) for asymptomatic enteric infection with NTS (eNTS) among Malawian children, followed by the development of first antigen-specific cellular immunity, and then functional systemic immunity. Systemic immunity is evidenced by the presence of anti-Salmonella LPS IgG antibody (αLPS IgG) which, when combined with complement opsonisation, results in functional protection, reflected in SBA. This is likely to be influenced by several factors, including social factors such as poverty and sanitation, by seasonal climatic conditions through the year, and by the impacts on immune status of malaria, malnutrition and anaemia. There is likely an interaction between several of these influencing risk factors.

**Figure 3. f3:**
[figure not shown]
Theoretical framework for a model of exposures and protection in iNTS disease.

**
*OptiVaNTS-Optimising Vaccination for iNTS disease in Africa*
**

Serum samples from SAiNTS will be used for systems serology analysis to map and define the mechanistic humoral correlates of immunity to invasive NTS.

### Contributing studies

**
*Malaria (RTS,S/ AS01) vaccine cluster randomised trial – EPI-MAL*
**

There is currently a phase 4 cluster randomised trial of the RTS,S/AS01 malaria vaccine being carried out in Chikwawa, Malawi, in which we will co-locate and embed the SAiNTS study. This offers a unique opportunity to explore the potential impact of the malaria vaccine on the development of the immune response to NTS, given that malaria has been shown to impair bactericidal activity (as described above).

### Nutrition and gut health

Myeloperoxidase (MPO) detected in stools is an indicator of intestinal inflammation and environmental enteric dysfunction, therefore understanding the association between MPO in stools and enteric NTS infections and acquisition of immunity to NTS can provide key insights into the mechanisms of disease susceptibility.

### Objectives

**
*Broad objective*
**

To understand the acquisition of immunity to NTS and epidemiology of eNTS in children 0–5 years, and how this immunity varies with risk factors (malaria, anaemia, malnutrition and sickle cell disease) and geographical setting.

**
*Specific objectives*
**

1.   To estimate the seroprevalence by age of NTS in children 0–5 years in Chikwawa, Malawi.

2.   To estimate the seroincidence by age of NTS in children 0–5 years in Chikwawa, Malawi.

3.   To explore the effect of the main risk factors: malaria, malnutrition, anaemia, and sickle cell disease on the acquisition of humoral immunity to NTS (IgG and SBA).

4.   To describe the relationship between IgG and SBA including effect modification by age.

5.   To estimate the age-stratified seroprevalence of Salmonella enteric infections (eNTS) by risk factor group: malaria, malnutrition, anaemia, and sickle cell disease.

6.   To compare age-stratified acquisition of immunity to NTS across sub-Saharan African settings (Vacci-NTS sites: Kenya, Malawi, Burkina Faso, Ghana).

**Exploratory objectives**

1.   To define an antibody CoP based on the inverse relationship between known age-stratified clinical disease incidence and age-stratified seroprevalence.

2.   To investigate the impact of malaria (RTS,S/ AS01) vaccination on age-stratified acquisition of bactericidal activity against NTS.

3.   To investigate how intestinal inflammation/ environmental enteropathy relates to enteric NTS infections and development of immunity.

4.   Understand antibody kinetics of immune response to NTS and
*Salmonella* Typhi in blood culture confirmed cases and community serosurvey samples to inform seroincidence estimates.

## Methods

### Study design

**
*Prospective community cohort*
**

We will carry out a prospective cohort study with paired serology samples at baseline and 3-months taken from the same individuals. Two thousand children aged 0–5 years sampled across age-strata will be recruited, randomly sampled throughout household-censused enumeration areas. We will spread sampling evenly throughout the year in Chikwawa district, Malawi, aiming to capture peak iNTS season in the middle of the study period. These children will be evenly recruited from the vaccinated (Montfort) and non-vaccinated clusters (Chikwawa) of the EPI-MAL trial. We will select households containing children 0–5 years via a two-stage sampling technique. In the first stage enumeration areas (EA) will be selected using probability proportional to size (PPS) sampling, with stratification according to malaria prevalence. In the second stage households containing children 0–5 years will be randomly sampled from selected Enumeration Area (EA). Any child eligible in the household will be invited to participate in the study.

We will collect approximately 2500 stool samples and 4000 paired blood samples (to account for 20% loss to follow-up), measuring antibody titres (IgG) and changes in serum bactericidal activity (SBA) for the most common NTS serovars (S. Typhimurium and S. Enteritidis) and other serovars, to understand the age-stratified acquisition of immunity and how this varies with risk factor exposure. We will perform anthropometric measurements, malaria (rapid diagnostic tests [RDT] and thick blood films), haemocue and sickle RDT to assess the association with the main risk factors. Any children found to have positive malaria tests will be provided treatment by the field team. Any child with a low haemoglobin will provided treatment according to the Integrated Management of Childhood Illnesses (IMCI)/ World Health Organisation (WHO) guidelines for management of anaemia
^
17
^ and referred to hospital for follow-up. A comprehensive record of the treatments administered throughout the study will be documented for subsequent analysis. Any child diagnosed with sickle cell disease or malnutrition (based on weight-for-height z-scores or Mid-Upper Arm Circumference (MUAC)) will be referred to the local health facility for further management.

Detailed immune and antigenic investigation of these samples will be carried out in collaboration with OptiVaNTS. An immune correlate of protection will be estimated using age-stratified acquisition of immunity and age-stratified incidence of clinical disease defined by routine blood cultures collected through MLW-Queen Elizabeth Central Hospital. Stool samples will be tested for salmonella culture and Polymerase Chain Reaction (PCR), which will enable us to model the effect of eNTS at visit 1 to induce systemic immunity at visit 2. Data will be collected on sociodemographics and indicators of water, sanitation and hygiene (WASH) using the REDCap and Open Data Kit (ODK) platforms (see
Table 1).

**Table 1. T1:** Summary of data to be collected.

Biological measure	Variable	Target n observations	Methods
Enteric Salmonella infections (usually transient & asymptomatic)	eNTS event	4000	Stool culture in selective broth, DNA extraction and qPCR for TTR gene.
Serological marker of invasive NTS infection	iNTS event	4000	ELISA for anti-S. Typhimurium and S. Enteritidis LPS IgG, conducted on 3-month paired serum samples.
Functional protective measure of serum killing	Serum killing	4000	Serum bactericidal activity high-throughput assay conducted on 3-month paired serum samples.
Rainfall and temperature	Climate	475 days	Daily measurements by Malawi Meteorological Office.
Poverty and sanitation	Poverty	4000	Validate questionnaire of household wealth and WASH (water, sanitation, and hygiene).
Current or recent malaria	MRDT	4000	Point-of-care fingerprick lateral flow antigen detection Malaria Rapid Diagnostic Test (P. falciparum HRP2 detection).
Haemoglobin	Hgb	4000	Haemoglobin (g/dl) measured by point of care fingerprick haemocue test.

We will compare the age-stratified acquisition of immunity (IgG and SBA) between children receiving the malaria vaccine (RTS,S/AS01) and un-vaccinated children matched on factors known to influence vaccine uptake. The EPI-MAL study has conducted a GPS-mapped household census, allowing us to randomly select children across the study age-strata to approach for recruitment. Selection of enumeration areas has assumed approximately 50% uptake of consent to the study, and statistical power calculations have assumed a further 10% drop out for the second visit.

Detailed schemas illustrating the rotation of field teams recruitment and sampling of stool and blood are shown in
Table 2 &
Figure 4 also see
full protocol (
*Extended data*)
^
6
^.

**Table 2. T2:** Detailed schema of SAiNTS field illustrating teams 3-monthly rotations through sequential enumeration clusters.

		**Q1, 2021**								**Q2, 2021**								** Q3, 2021**								**Q4, 2021**								**Q1, 2022**									**Q2, 2022**			
		**V1 C1**									**V2 C1**									**V2 C2**									**V2 C3**									**V2 C4**								
											**V1 C2**									**V1 C3**									**V1 C4**																	
**RTS,S unvaccinated**	1																																													
High malaria	2																																													
prevalence	3																																													
(Chikwawa)	4																																													
N=1200	5																																													
	6																																													
	7																																													
	8																																													
	9																																													
**RTS,S vaccinated**	10																																													
Low malaria	11																																													
prevalence	12																																													
(St Montfort)	13																																													
N=1200	14																																													
	15																																													
	16																																													
	17																																													
	18																																													

Scheme showing sampling rotation through enumeration areas (EAs) (1 to 18), with four cohorts (C1 to C4) starting at 3 monthly time intervals in each of the high and low malaria transmission areas. Each EA will be visited at four time periods throughout the year, to capture variations in seasonality. A total of 2400 children will be recruited, 1200 at each site, with 30-40 children recruited over 7-12 days at each EA at each round of recruitment. Each child will have paired samples collected 3 months apart, and the next cohort of children will be recruited at the same time as the day 90 follow-up at each EA.

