**Figure 7. f7:**
[figure not shown]
**A**: Power for detecting change in SBA due to malaria infection.
**B**: Example of data from a single simulation (malaria).
**C**: Power curves for detecting impact of anaemia on mean NTS antibody level.

**Table 4. T4:** Summary of all sample size calculations carried out by risk factor and outcome.

Risk factor	Prevalence	Difference in SBA between 3 monthly samples (CFU/ml)	Difference in antibody titer	Difference in seroconversion over 3 months	Power to detect effect
*Malaria*	16%	0.25	13		>=80%
*Moderate to severe anaemia*	20%	0.225	13		>=80%
*Malnutrition*	2%	0.65	47		>=80%
*Sickle cell disease*	1%	0.9	68		>=80%
*Enteric NTS infection*	8%	0.2	15	15–20%	>=80%/ 99.97%
*Malaria RTS,S/AS01 vaccination*	60% coverage	1.5	-	-	>=80%

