### Statistics and analysis

**
*Description of statistical methods*
**

Data analysis will be carried out using the R environment for statistical computation
^
20
^. We will use changes in SBA along with OAg IgG as the primary measures of immunity in a modelling framework we have already developed, that combines censored regression with linear or cubic splines and allows principled change point analysis
^
21,
22
^ to identify the age of antibody and SBA nadir for each serovar. We will use this model to describe the impact of age, malaria exposure (MRDT), malnutrition, anaemia and eNTS exposure on SBA and OAg IgG. The models we develop will account for correlations between the paired samples using generalised estimating equations. Regression coefficients and confidence intervals will be calculated for each of the risk factors; malaria RDT positivity, MUAC, haemoglobin, and adjusted for season, poverty and sanitation. Percentage change in IgG and SBA between paired samples will be calculated, plotted against age and compared by season, using generalised linear models. Number of seroconversions by age will be calculated, with the seroconversion defined by fold-increases in IgG or SBA. The sero-incidence rates will be compared across risk factor groups and by season. Finally, additional contrasting datasets (cross-sectional sample sets from vacciNTS sites in Burkina Faso, Ghana and Kenya) will allow us to compare immunological markers in different settings.

As an exploratory analysis, mechanistic mathematical models will be developed to identify a population correlate of protection using acquisition of IgG and SBA by age with rates of invasive NTS disease by age. Additional exploratory analyses will include impact of RTS,S malaria vaccination on the development of immune response to NTS, graphical models (Bayesian networks, structural equation models or Gaussian copula graphical models), to interrogate the complex relationships between the immunological and environmental variables; and geospatial analyses of the GPS-mapped subject and household data.

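### The RTS,S contrast carries site and malaria level with it unless unvaccinated controls come from within Montfort, and site is missing from the named adjusters

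*Protocol article*

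**What the plan says.** - **Recruitment (Study design, prospective community cohort):** "These children will be evenly recruited from the vaccinated (Montfort) and non-vaccinated clusters (Chikwawa) of the EPI-MAL trial".
- **Table 2:** EAs 1-9 are labelled "RTS,S unvaccinated", high malaria prevalence, Chikwawa, N=1200. EAs 10-18 are labelled "RTS,S vaccinated", low malaria prevalence, St Montfort, N=1200. The footnote describes the cohorts as starting "in each of the high and low malaria transmission areas".
- **Vaccine comparison (Study design, after Table 1):** children who received RTS,S are to be compared with "un-vaccinated children matched on factors known to influence vaccine uptake". The article does not say from which area those children are drawn.
- **Risk-factor models (Statistics and analysis):** coefficients for malaria RDT positivity, MUAC and haemoglobin are to be "adjusted for season, poverty and sanitation". Site is not named.
- **Table 4:** the row "Malaria RTS,S/AS01 vaccination" gives 60% coverage and an SBA difference of 1.5 at 80% power or more.
- **Status:** the vaccine question is exploratory objective 2. The section on contributing studies gives its rationale: malaria impairs bactericidal activity.

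**The concern.** No EA is both vaccinated and high-malaria, and none is both unvaccinated and low-malaria. By the protocol's own premise, less malaria should mean better bactericidal activity, and the vaccinated area is the low-malaria one. That mechanism alone pushes a Montfort-Chikwawa difference towards an apparent vaccine benefit, even if the vaccine does nothing for immunity to NTS. Differences in sanitation or Salmonella exposure between the two places could add to it or offset it.

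The stated remedy, matching on factors that influence uptake, deals with who gets vaccinated where vaccine is offered. It does not deal with differences between the two places. Because the parent study is described as cluster randomised, readers may also give the contrast a causal weight that this layout cannot bear.

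A lesser form of the problem reaches specific objective 3. RDT positivity should differ between areas labelled high and low prevalence. With site out of the model, the malaria coefficient can absorb part of any site or vaccine difference.

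**Working it through.** **1. Area level.** Inputs are the Table 2 labels, with 1,200 children per area. A model with intercept, site and area-level vaccination has three columns but rank 2. Adding malaria level gives four columns, still rank 2. A larger sample, or more EAs in the same two places, does not change this.

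**2. Child level.** Assume coverage c in Montfort and none in Chikwawa. Table 4 gives c = 60%; I show 40% to 80%. Intercept, site and child-level vaccination then have rank 3 of 3, so the vaccine coefficient can be estimated with site in the model.

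Let D be the non-vaccine difference between the sites.
- Controls from Chikwawa only: the contrast carries 100% of D.
- All unvaccinated children pooled: it carries 1200 / [1200 + 1200(1 − c)] = 1/(2 − c) of D. At 60% this is 1200/1680 = 71%.
- Controls from Montfort only: it carries none of D.

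The squared correlation of vaccination with site is c/(2 − c), and the variance inflation from adding site is 1/[1 − c/(2 − c)].

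| Coverage | Vaccinated | Unvaccinated in Montfort | All unvaccinated | Share of D if pooled | Variance inflation |
|---|---|---|---|---|---|
| 40% | 480 | 720 | 1920 | 63% | 1.33 |
| 60% | 720 | 480 | 1680 | 71% | 1.75 |
| 80% | 960 | 240 | 1440 | 83% | 3.00 |

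**3. What the within-Montfort contrast can detect.** Assume two-sided alpha 0.05 (not stated in the article), 80% power, no clustering and no dropout. The detectable difference is 2.802 × SD × √(1/720 + 1/480) = 2.802 × SD × 0.0589. At SD 0.4, which the article states only for the eNTS calculation, this is 0.066. At an assumed SD of 1.6 (step 4) it is 0.26.

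**4. The Table 4 vaccination row.** The row gives no SD or model, so 1.5 cannot be reproduced. It can be compared with the other SBA rows. The text on SBA by age and the Figure 8D caption give N = 2500. The implied SD under a simple two-group formula is difference / [2.802 × √(1/n₁ + 1/n₂)]:

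| Row | n₁ v n₂ | Difference | Implied SD |
|---|---|---|---|
| Malaria, 16% | 400 v 2100 | 0.25 | 1.64 |
| Anaemia, 20% | 500 v 2000 | 0.225 | 1.61 |
| Malnutrition, 2% | 50 v 2450 | 0.65 | 1.62 |
| Sickle cell disease, 1% | 25 v 2475 | 0.9 | 1.60 |
| RTS,S, 60% | 1500 v 1000 | 1.5 | 13.1 |

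Four rows agree on an SD near 1.6. With that SD, a 60/40 split would detect 2.802 × 1.6 × √(1/1500 + 1/1000) = 0.18. A near-balanced exposure is thus given a larger detectable difference (1.5) than one present in 1% of children (0.9).

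**5. The malaria coefficient.** The exposure is each child's RDT result, which can vary within both areas, so it is not collinear with site. The article gives 16% prevalence overall and no figure by area, so the share of D that this coefficient absorbs cannot be calculated.

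**The case against.** The strongest reply is that the planned comparison is between children, not areas. Coverage is 60%, the unvaccinated children are to be matched, and nothing says they must come from Chikwawa; the full protocol, which is not shown, may settle this. That stands. A reader might infer from Table 2 that no vaccine effect can be estimated at all. The documents do not support this, because step 2 shows that a within-Montfort contrast exists.

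The reply also holds on four further points.
- **Status.** The vaccine question is exploratory, so no specific objective fails because of it.
- **Malaria coefficient.** A reader might infer that it is confounded to the same degree as the area contrast. It is not: RDT status is measured on each child, and the models already adjust for poverty and sanitation.
- **Table 4.** A reader might infer that the 1.5 row is wrong. That is not shown. A difference of 1.5 does give at least 80% power (about 100% at SD 0.4). The sample sizes were simulated, and a different model may lie behind this row.
- **Malaria level.** The article does not say whether Montfort's low prevalence was measured before vaccination. If it is partly a vaccine effect, adjusting for it would remove some of the effect sought.

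None of this rescues a contrast whose controls come wholly or mainly from Chikwawa. Leaving the source of controls open also leaves open whether the bias is none, most or all of the site difference.

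**Conclusion.** At area level, RTS,S vaccination is fully confounded with site and malaria prevalence. The planned vaccine contrast carries all of any non-vaccine site difference with Chikwawa-only controls, and about 71% with pooled controls (63% to 83% for coverage of 40% to 80%). These figures assume 1,200 children per area and no vaccination in Chikwawa. Matching on uptake factors and adjusting for season, poverty and sanitation leave other place differences in.

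The conclusion is limited. A vaccine contrast within Montfort can be estimated, though it is observational. The malaria coefficient in specific objective 3 is open to partial confounding by site, of unknown size. The 1.5 in Table 4 is out of line with its neighbours and unexplained.

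**What to change.** 1. Add site, which in Table 2 coincides with the malaria sampling stratum, to the risk-factor models alongside season, poverty and sanitation. This uses one parameter and needs no new data.
2. For exploratory objective 2, make the main contrast vaccinated against unvaccinated age-eligible children within Montfort, matched or adjusted on age and uptake factors. State the source of the controls.
3. State that the Montfort-Chikwawa difference is a comparison of places, not a randomised or vaccine effect. Do not adjust for area malaria level as a baseline confounder unless it was measured before vaccination.
4. Explain the 1.5 in Table 4 by giving its SD and model, or recompute it for the contrast in item 2.

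A difference-in-differences against Chikwawa, using age groups never eligible for the vaccine, may look attractive. The article gives no eligibility ages, so it should be added only if such groups are documented.

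**Cost.** This is mainly analysis wording. Table 1 does not list individual vaccination status, so the sponsor should confirm that it is recorded. The vaccine contrast shrinks to at most about 720 against 480 children at an assumed 60% coverage of 1,200, and to fewer once age-ineligible children are removed. Confounding by uptake will remain and should be stated as a limitation.
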